**Fig. 1 Fig1:**
[figure not shown]
Standard protocol items: recommendation for interventional trials (SPIRIT) figure illustrating the timeline for enrolment, interventions and assessments in the trial. ZMC zygomaticomaxillary complex; ZA zygomatic arch; CT computed tomography; SMV submental vertex; PA posterior anterior; OM15/OM30 occipitomental 15/30 degrees; LOS length of surgery

If there is any alteration to the trial protocol that has been submitted to the RBWH Human Research Ethics Committee and the Australian and New Zealand Clinical Trials Registry, these organisations will be informed of the amendments immediately.

### Recruitment and consent

All patients who present to the OMFS of the RBWH, with an isolated ZMC fracture or an isolated ZA fracture, will be screened for a position on the trial. As RBWH is an adult hospital, all patients will be 16 years of age or older and they must require surgical management of their ZMC or ZA fracture to be included in the trial. Criteria for exclusion from the trial include the following:
PregnancyInability to give informed consentConcomitant non-zygomatic facial fractures (including orbital floor fractures) or bilateral zygomatic fracturesNot wishing to be part of the study

If a patient fulfils the criteria to participate in the trial, they will be informed verbally of what the trial involves, the risks associated with it and their role. They will also be given written information on the trial, the risks involved and all of their rights, including the ability to withdraw at any stage. If the patient is happy to participate, they will be given a consent form to complete. The aforementioned tasks of obtaining informed consent and recruiting patients to the trial will be completed by an oral and maxillofacial surgery registrar (training surgeon) or consultant (surgeon).

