### Randomisation

The patients who are recruited to the trial will be randomised into two groups, intraoperative computed tomography scan (intervention) and no intraoperative computed tomography scan (control). The patient will be randomised by the oral and maxillofacial surgery department nurse, who will blindly select a table tennis ball from a container. The container will hold only two balls, with one ball having the word “intervention” and the other ball having the word “control” written on them. Whichever ball is selected by the nurse, is the group to which the patient is allocated.

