### Study groups (control and intervention)

The intervention group will undergo CT during their operation to reduce the ZMC or ZA fracture. This scan occurs after the fracture has been opened, reduced and fixated or in the case of an isolated zygomatic arch fracture, after it has been opened and elevated. Once the scan has been completed the surgeon will review the scan and decide if the reduction is satisfactory. If they are satisfied with the reduction, the incisions will be closed and the operation completed. If there are inaccuracies with the reduction, the fixation equipment will be removed and the fractured bone adjusted to the correct position. It is then left to the discretion of the surgeon to decide if they wish to have another intra-operative CT scan or if they are clinically satisfied with the reduction. Once the surgery is completed, post-operative radiographs will be performed prior to the patient being discharged home. These radiographs will include a submental-vertex view (SMV), a posterior-anterior face (PA face) view and occipitomental 15° and 30° views (OM15 and OM30).

Patients in the control group will undergo their relevant surgery as normal but will not have any intra-operative imaging performed. After completion of the surgery, control group patients will undergo the same post-operative radiography as described for the intervention group. No other concomitant care or interventions are prohibited during the trial.

Surgical incisions are identical in both groups but are at the discretion of the operating surgeon. Direct access to fracture sites is via the upper blepharoplasty incision, subtarsal incision or upper buccal sulcus transoral incision. Elevation is either via a “Gillies” temporal incision or upper buccal sulcus incision.

All procedures will be performed by or under the direct in-theatre supervision of one of three Oral and Maxillofacial Specialist surgeons. All three have extensive experience in the management of facial trauma with each having a minimum experience of managing 300 hundred zygomatic complex fractures.

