### Follow up and outcomes

All patients in the trial will have post-operative SMV, PA face, OM15 and OM30 radiographs taken either on the day of surgery or on the following day, prior to discharge. These radiographs will be assessed blinded to study group, by an oral and maxillofacial surgeon who will not be involved in any of the operations or pre-surgical or post-surgical clinical assessments. The adequacy of the fracture reduction will be based on the radiographs and the quality of the reduction will be evaluated as “good”, “fair” or “poor”:
Good: equivalent to premorbidFair: minor discrepancy but unlikely to require re-operationPoor: major discrepancy, re-operation required

Patients in the trial who are undergoing ZMC open reduction and internal fixation will stay overnight in hospital, and barring any complications will be discharged home on day 1 post-surgery. Patients undergoing open reduction of their isolated ZA fracture will be discharged on the same day as surgery, unless there are any unforeseen complications. All patients will be followed up in the OMFS outpatient department at 1 week and 6 weeks post-surgery. During these outpatient appointments, the registrar or consultant reviewing the patient will assess them for diplopia, surgical site scarring and facial profile restoration. These parameters will be graded by the OMFS registrar or consultant and their assessment will be recorded on a standardised form (Figs. 2 and 3). The need for revision surgery at any timepoint until 3 months following the completion of the study and a number of other variables (see Figs. 2 and 3 for a full list) will also be recorded on the form.

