### Evaluation of outcomes

The two-sample *t* test will be used for analysis of continuous variables. The chi-square test will be used for analysis of categorical variables and for all data, a *p* value <0.05 will be considered significant. The software program SPSS will be used for all statistical analysis. Subgroup analysis based on the severity of the fractures will also be conducted. Patients will be analysed as per their treatment but non adherence will be considered in the final presentation of data. An interim analysis will be also be undertaken. There are no other audits of trial conduct planned.

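### Two different operations are pooled and compared with unadjusted tests; fracture type, known at screening, is not used, which costs precision mainly on length of surgery

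*Protocol article*

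**What the plan says.** Under Recruitment and consent, patients "with an isolated ZMC fracture or an isolated ZA fracture, will be screened for a position on the trial". Both types enter one trial with one pair of arms.

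The document treats the two as different operations. Under Study groups (control and intervention), the point at which the intra-operative scan is taken depends on the type: "opened, reduced and fixated or in the case of an isolated zygomatic arch fracture, after it has been opened and elevated". Under Follow up and outcomes, "Patients in the trial who are undergoing ZMC open reduction and internal fixation will stay overnight in hospital", whereas "Patients undergoing open reduction of their isolated ZA fracture will be discharged on the same day as surgery", in both cases barring complications.

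Allocation does not take account of type. Under Randomisation, "The container will hold only two balls, with one ball having the word “intervention” and the other ball having the word “control", and the ball drawn decides the group.

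Under Evaluation of outcomes, "The two-sample *t* test will be used for analysis of continuous variables" and the chi-square test is used for categorical variables. No covariate or stratum is named. One subgroup is planned: "Subgroup analysis based on the severity of the fractures will also be conducted". Severity is not defined there, and fracture type is not mentioned.

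**The concern.** Fracture type decides which operation is done, so it probably predicts several outcomes strongly, and operating time most of all. It has to be established at screening, because eligibility depends on it. It is therefore a baseline factor available for every patient before randomisation. The stated tests leave the difference between types in the error term, and the unstratified draw does not balance it between arms.

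Two things are at stake. The first is precision: a real effect on length of surgery, a secondary objective, could be missed because variation between operations swamps it. The second is interpretation: if CT helped in only one fracture type, the pooled result would average that with no effect in the other, and no stated analysis would show it.

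The tests are written into the article, so this is a chosen method that can be improved and not a detail left out.

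**Working it through.** **The plan's own figure.** Power calculation gives 200 patients, two-sided, 80% power, driven by radiographic reduction. No rates are stated, so 200 can be neither reproduced nor refuted. It fits many pairs of rates of good reduction, for example 50% vs 69.4%, 70% vs 86.3% or 90% vs 99%, each giving a total of 200 without continuity correction.

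**1. Length of surgery**

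Inputs from the document: expected increase 10 min (Ethical considerations); 200 patients, so about 100 per arm; two-sided 0.05.

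Assumed, because the document gives none: within-type SD 25 min (ZMC) and 10 min (ZA); arch share z from 0.1 to 0.4; gap g in mean duration between types from 30 to 60 min.

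- Within-type variance: W = (1 − z)·25² + z·10²
- Variance faced by the unadjusted t test: T = W + z(1 − z)·g²
- Power = P(Z > 1.96 − 10/√(2V/100)), with V = T unadjusted and V = W adjusted for type

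Worked case, z = 0.3, g = 60:

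- W = 0.7·625 + 0.3·100 = 467.5
- z(1 − z)·g² = 0.21·3600 = 756, so T = 1223.5
- Unadjusted: standard error √(2·1223.5/100) = 4.95, power about 52%
- Adjusted: standard error √(2·467.5/100) = 3.06, power about 90%

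| Arch share | Unadjusted, g = 30 | Unadjusted, g = 60 | Adjusted |
|---|---|---|---|
| 10% | 79% | 66% | 84% |
| 20% | 78% | 57% | 87% |
| 30% | 79% | 52% | 90% |
| 40% | 80% | 51% | 93% |

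The variance ratio T/W runs from 653.5/572.5 = 1.14 (10%, 30 min) to 1279/415 = 3.08 (40%, 60 min).

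A second set of assumptions uses one SD for both types and arch shares of 20–30%, with the same 30–60 min gaps:

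| Common SD | Unadjusted | Adjusted |
|---|---|---|
| 20 min | 55–86% | 94% |
| 25 min | 48–72% | 81% |
| 30 min | 41–59% | 65% |

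The direction is the same throughout; the size depends on the inputs.

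**2. Radiographic reduction (good vs not good)**

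Assumed ZMC rates are 70% vs 86.4%, which give 81% power at 100 per arm with no arch patients.

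- *Same odds ratio in both types.* The odds ratio is (0.864/0.136)/(0.70/0.30) = 2.72. With a ZA control rate of 50–90% and an arch share of 10–40%, unadjusted and stratified power differ by at most about 2 points. At a 30% share and a 90% ZA control rate they are 70.3% and 71.8%. At a 30% share and a 50% ZA control rate, pooled power is 84%, above the 81% with no arch patients.
- *Effect in ZMC only.* The pooled risk difference is (1 − z)·16.4 points, which is 11.5 points at z = 0.3. Pooled power falls to 71–74% (10% share), 59–65% (20%), 47–56% (30%) and 36–46% (40%), for a ZA rate of 70–90% in both arms.

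**3. Validity**

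Simulating 400,000 trials of 200 patients with simple randomisation, a 25% arch share and no CT effect, the pooled chi-square test rejected in 5.0–5.1% of trials. The test keeps its level.

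**4. Chance imbalance**

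The standard error of the difference in arch share between arms is √(2z(1 − z)/100). For z = 0.2 to 0.3 this is 5.7 to 6.5 points, so a gap of 10 points or more has a probability of about 8–12%.

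**The case against.** The strongest reply is that nothing here is invalid. The primary objective under Study objectives poses one joint question about ZMC and ZA fractures, the pooled difference answers it for the enrolled mix, and the test keeps its level. That stands.

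A reader might infer that real effects are diluted and obscured. The document does not support this. Dilution needs a smaller CT effect in one type, and no section states one. Study groups applies the same sequence to both types: scan, review, correct if inaccurate. Background gives limited visualisation as the reason for imprecise reduction in both. Dilution is a possibility, not a finding.

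A reader might also infer that arch fractures yield almost no diplopia, that access routes divide by fracture type, or that a re-reduction count means nothing without fixation. None of these is in the document. Background lists restricted eye movement as a consequence of inadequate reduction without separating the types, the incisions are listed without being assigned to a type, and an elevated arch can be elevated again. There is therefore no basis for restricting any outcome to ZMC patients.

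It can also be said that the large power figures concern a secondary objective and rest on assumed inputs. That is correct: on the outcome that sets the sample size the loss is small under a common odds ratio. Finally, covariates and the definition of severity may sit in an analysis plan that is not shown. That limits the point but does not remove it, because the article does state unadjusted tests.

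**Conclusion.** The point holds as one of efficiency and interpretation, not of bias. A likely strong prognostic factor, known before randomisation, is used neither in allocation nor in the stated tests, and the severity subgroup does not clearly stand in for it; a subgroup would not adjust the main comparison in any case.

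The cost falls mainly on length of surgery: a loss of about 5 points of power (10% arch share, 30 min gap) to about 43 points (40%, 60 min) in the main grid. These figures depend wholly on the assumed SDs, arch share and gap. On radiographic reduction the loss is at most about 2 points under a common odds ratio. If CT worked in ZMC fractures only, pooled power at a 30% arch share would be 47–56% instead of 81%, and the stated analyses would not reveal why. Worth changing, because the remedy costs almost nothing.

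**What to change.** In Evaluation of outcomes, include fracture type at screening (ZMC or isolated ZA) as a covariate or stratum in the between-arm comparisons:

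- a linear model with arm and fracture type for length of surgery;
- Mantel-Haenszel or another stratified test for yes/no outcomes;
- stratified or ordinal regression for graded outcomes such as radiographic reduction.

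Report the CT effect for each fracture type with an interaction estimate, labelled as supportive. Keep all randomised patients in every primary comparison, and restrict no outcome to one type.

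The change is to analysis wording only. Fracture type is already established for eligibility, so no patients, visits or procedures are added. The downside is that arch-only estimates will be imprecise and should be presented with their confidence intervals, not as separate tests.

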### Randomisation

The patients who are recruited to the trial will be randomised into two groups, intraoperative computed tomography scan (intervention) and no intraoperative computed tomography scan (control). The patient will be randomised by the oral and maxillofacial surgery department nurse, who will blindly select a table tennis ball from a container. The container will hold only two balls, with one ball having the word “intervention” and the other ball having the word “control” written on them. Whichever ball is selected by the nurse, is the group to which the patient is allocated.

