### Blinding

The patients will not be informed of the group to which they are randomised. Concurrently, the clinician assessing the fracture reduction on the post-operative radiographs will be blinded to the arm of the trial to which the patient has been allocated. The surgeon operating on the patient will not be blinded as this is impossible, given they will be witness to whether or not intra-operative CT is performed. The physician assessing the patient in clinic at both 1 week and 6 weeks post-surgery will not be blinded to the patient’s study group. Blinding of this assessment would be extremely difficult as the physician assessing the patient will be involved with the operation and hence know the allocated group. The clinician assessing the post-operative radiographic reduction will not perform any of the operations in the trial.

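### Allocation by a nurse's hand draw of one of two balls leaves no sequence to check, so a repeated or discarded draw could be neither prevented nor detected

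*Protocol article*

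**What the plan says.** The Randomisation section of the protocol article describes the procedure. The oral and maxillofacial surgery department's nurse is the person "who will blindly select a table tennis ball from a container. The container will hold only two balls", one labelled for each arm. The rule is then: "Whichever ball is selected by the nurse, is the group to which the patient is allocated". The section mentions no sequence prepared beforehand, no witness and no stratification factor, and it does not say whether the ball is put back before the next patient.

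Other sections supply the setting:

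- **Recruitment and consent:** registrars or consultants of oral and maxillofacial surgery recruit patients and take consent.
- **Blinding:** the operator knows the arm ("The surgeon operating on the patient will not be blinded as this is impossible"). So does the clinic assessor, because "the physician assessing the patient will be involved with the operation and hence know the allocated group". The radiograph reader is blinded and performs none of the operations.
- **Follow up and outcomes:** diplopia, scarring and facial profile are graded in clinic by a registrar or consultant.
- **Evaluation of outcomes:** the tests named are the two-sample t test and the chi-square test, with a subgroup analysis by fracture severity. Apart from the interim analysis, no audits of trial conduct are planned.
- **Power calculation:** about 200 patients in total.

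**The concern.** Randomisation protects against selection bias only if nobody can change an allocation once it is made, and a reader can rely on it only if this can be checked afterwards. A hand draw fails the second condition and weakens the first. If an unwelcome ball were put back and drawn again, the only trace would be the result that was finally written down.

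This matters more here because the nurse who draws works in the department whose clinicians recruit, operate and grade three of the outcomes unblinded. For those outcomes, sound allocation is one of the few protections left. The blinded radiograph reader does not help with this, since blinding the reader cannot undo a difference between the arms in the patients who entered them.

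The silence on returning the ball is a second, smaller problem. The two possible procedures have very different properties, and the text should not leave the choice open.

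**Working it through.** **Inputs.** From the protocol article: two balls, one per arm; 200 patients; two-sided testing at 0.05 with 80% power. Assumed, because the article gives no figures: the number of isolated zygomatic arch (ZA) patients and the rates of good reduction. The total of 200 cannot be reproduced without outcome rates. It is used here only as a scale.

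**1. Can a draw be verified?** With a list fixed in advance, the k-th patient's recorded arm can be compared with the k-th entry. With a ball draw there is no k-th entry. A log of results, if one is kept, records what was reported and cannot show that it was the first draw. This holds whether or not the ball is returned.

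**2. Predictability if the ball is returned.** Each allocation is an independent 50:50 draw. A best guess is right 50% of the time.

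**3. Predictability if the ball is left out.** Allocations come in fixed blocks of two. The second of each pair is certain: 200 / 2 = 100 patients, or 50%. Best-guess accuracy = 0.5 × 0.5 + 0.5 × 1 = 75%.

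**4. Arm sizes if the ball is returned.** With X ~ Binomial(200, 0.5):

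- P(arms differ by 20 or more, that is 110:90 or worse) = 0.179
- P(arms differ by 28 or more, that is 114:86 or worse) = 0.056

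Relative efficiency is 4ab/(a+b)²: 4 × 90 × 110 / 200² = 0.99, and 4 × 86 × 114 / 200² = 0.98. Under assumed rates of 70% and 86.3%, which fit 100 per arm at 80% power, power is 0.801 at 100:100, 0.802 at 90:110 and 0.800 at 86:114. The cost is negligible.

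**5. Fracture-type imbalance if the ball is returned.** For an assumed 40 ZA patients, P(24:16 or worse) = 0.268. For 50, P(30:20 or worse) = 0.203. A 24:16 split in arms of 100 is an 8-point difference in ZA share. If good-reduction rates differed by 20 points between zygomaticomaxillary complex (ZMC) and ZA fractures (assumed), the arm difference would move by 0.08 × 20 = 1.6 points. The effects that 100 per arm can detect, for assumed lower rates of 50% to 80%, run from 69.4 − 50 = 19.4 points down to 93.4 − 80 = 13.4 points.

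**6. Would small permuted blocks be better?** Suppose the guesser always names the arm that is behind. The expected number of correct guesses in a block of 2m is m + (4^m / C(2m, m) − 1)/2.

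- Block of 4: 2 + (16/6 − 1)/2 = 2.83, or 71%
- Block of 6: 3 + (64/20 − 1)/2 = 4.10, or 68%
- Blocks of 4 and 6 chosen at random with equal chance: (2.83 + 4.10)/10 = 69%; simulation at n = 200 also gives 69%

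For someone who can follow past allocations, small blocks are therefore more predictable than a draw with the ball returned.

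**The case against.** The strongest reply is that this is simple randomisation, which is valid. The text speaks of selecting from a container that holds two balls; if one had been left out there would be nothing to select for the next patient. Both balls are therefore most naturally present each time, and nothing can be predicted. A nurse, not the recruiter, makes the draw, and only for patients already recruited. A draw log may exist in the full protocol, which a journal article condenses. Recruitment began in August 2016 and was expected to finish in September 2019, so a change may come late.

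Much of this stands, and it rules out several stronger readings that a reader might infer:

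- **That half the allocations are predictable.** This follows only if the ball is left out, which the text neither says nor favours.
- **That the recruiting surgeons see every allocation.** No section says so. The operator and the clinic assessor know the arm of the patients they treat. Recruiters come from the same department's registrars and consultants, but the article does not say that one person both recruits and operates on a given patient.
- **That no record of draws is kept.** The article is silent, and silence in a condensed article is not evidence.
- **That lack of stratification or unequal arms biases the trial.** Chance imbalance is already allowed for in the test's error rate, and steps 4 and 5 show that its effect is small. A subgroup analysis by severity does not require stratified allocation.

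The reply does not reach the central point. The article states the mechanism itself, and a draw cannot be checked against anything, with or without a log.

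**Conclusion.** The concern holds in a limited form. The stated method gives no means of preventing or detecting a repeated or discarded draw, in a trial where one department recruits, allocates, operates and grades clinic outcomes unblinded, and where no audit of conduct beyond the interim analysis is planned. The documents do not suggest that any draw was tampered with; the weakness is that its absence could not be shown. The size of any resulting bias cannot be calculated.

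Predictability is conditional: none if the ball is returned, which is the natural reading, and 100 of 200 allocations certain if it is not. Chance imbalance is secondary. The figures for fracture type rest on an assumed 40 to 50 ZA patients and an assumed 20-point difference in outcome, and even then the shift of about 1.6 points is small beside the effects that the trial could detect.

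**What to change.** For patients not yet allocated, replace the draw with a computer-generated sequence prepared by someone outside the department, for example the biostatistician who did the power calculation. Hold it in sequentially numbered, opaque, sealed envelopes or in a web tool. The same nurse opens the next allocation only after consent and study number have been logged with date and time.

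Use simple randomisation, or large blocks of randomly varied size that are not disclosed to the department. Avoid small blocks such as 4 and 6, for the reason in step 6 of the working. Stratification by ZMC versus ZA is optional.

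Adjust the main reduction analysis for fracture type (ZMC versus ZA), for example with a test stratified on it. State in the Randomisation section whether balls were returned for patients already allocated. Those patients keep their allocation, and the report gives the change of method and its date.

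The cost is a few hours of statistician time and an amendment notified to the ethics committee and the registry, with no extra staff. The new sequence protects only the remaining patients. If recruitment is too far advanced for it, the statement on returned balls and the adjustment for fracture type are still worth making.
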